### Study design

The Institutional Review Board of the Second Affiliated Hospital and Yuying’s Children Hospital, Wenzhou Medical University, China, approved this study. Prior to inclusion, all subjects will be informed about the objectives and procedures of the study. Subjects who meet the inclusion criteria must provide informed consent before entering into the study.

Subjects (*n* = 60) diagnosed with stoke in its subacute stage (defined as more than 1 week and less than 12 weeks after stroke onset) from an in-patient stroke rehabilitation unit in China will be enrolled in a single-blinded randomized controlled trial for 15 weeks. They will be randomized in a 1:1 fashion into (1) a new 3-week rehabilitation training program with an immersive VR system, (2) a 3-week conventional rehabilitation program. The random allocation will follow a covariate-adaptive randomization procedure [34, 35]. Each subject will be randomly assigned a code based on computer-generated, stratified, permuted block randomization with a block size of 8 and balanced by age and location of stroke.

All subjects will receive three assessments at the following time points: immediately following enrollment but before randomization (week 0), immediately following conclusion of the randomized rehabilitation program (week 3) and follow up 12 weeks after conclusion of the rehabilitation program (week 15). The assessment includes inclusion and exclusion of subjects, clinician-filled questionnaires and MRI scans. To avoid assessment bias, all inclusion and exclusion assessments and clinician-filled questionnaires will be completed by physiotherapists who are blinded to this study and with at least 2-years of experience in physical therapy. The flow chart for the study is shown in Fig. 1 and the schedule of enrollment, interventions, and assessments of the study (as recommended by Standard protocol items: recommendation for interventional trials (spirit) 2013 [36]) is shown in Fig. 2.

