### Sample size considerations

This randomized controlled trial is a two-group independent design examining the effects of immersive VR on rehabilitation of subjects with subacute stroke. We assumed a two-tailed comparison and set the type I error rate at 0.05 with 80% power. We plan to screen approximately 100 individuals with subacute stroke. After screening, 80 subjects will be recruited and randomized to the experimental group or the control group. As a conservative estimate (dropout rate = 25%), we presume that 60 subjects will complete the study. To reduce the dropout rate, we will employ two strategies to keep participants engaged: regular communication via phone or social media and clinician visits. After conducting a power analysis based on the aforementioned statistical parameters using the software GPower3.1.9.2 [39], the effect size is calculated as 0.74, which is between a medium (0.5) and large (0.8) effect size [40]. Moreover, there is evidence from a small sample (8 subjects) that VR-enhanced treadmill training for 5 sessions per week over 3 weeks induces significant cerebral reorganization [41]. Thus, 30 subjects for one group is sufficient to assess the effectiveness of immersive VR training in post-stroke rehabilitation in eliciting upper-limb motor recovery post-stroke compared to traditional rehabilitation training, and to investigate the underlying brain mechanisms of immersive VR-based rehabilitation using three MRI modalities.

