### MRI data processing

Data quality control: each imaging modality (T1, RS-fMRI and DTI) will undergo quality control and data with excessive motion or bad signal-to-noise ratio will be excluded [48]. Three different metrics are evaluated for each subject: (1) for T1, the volume of seven regions of interest (ROIs) and the stretch factor (transformation required to move the native-space in the brain to template space) is obtained; (2) for RS-fMRI, the temporal signal-to-noise ratio is calculated; and (3) for DTI, the mean fractional anisotrophy (FA) and mean diffusivity is obtained for specific ROIs and for white matter. These metrics must be met for the obtained scans to be accepted and to start the analysis for each modality.

The subjects’ structural T1 images will be analyzed using the FSL subcortical segmentation tool “FIRST” [49] and with the FSL gray matter density tool “VBM” [50]. From the results of FIRST, which includes 14 subcortical regions, and structural connectivity that correlates in 360 parcellations of cerebral cortex [51], we will find ROIs that may correlate with rehabilitation performance and continuing performance. Meanwhile, from the VBM result, the significant difference in local gray matter regions will be evaluated.

The subject’s RS-fMRI will be analyzed using FSL tools. First, we will use an independent component analysis (ICA)-based strategy for automatic removal of motion artifacts (AROMA) [52] to pre-process the data and correct resting images for motion. Second, we will regress out any signal found in ventricles and in white matter as these are considered artifacts. We will also remove the whole-brain global signal. To allow comparison between subjects, these filtered functional data will be registered to a standard brain and down-sampled to a 6 × 6 × 6 mm voxel size. A program produced in house called Apkarian Brain Linkage Mapping (ABLM), described and reported by Baria [53], will be used to provide the number of functional connectivity links of each brain voxel.

The subject’s DTI will be analyzed using FSL tools. We will use the diffusion toolbox “FDT” [54] to pre-process the DTI images. First, we will correct each subject’s DTI images for “eddy current” and then apply a “dtifit” algorithm to obtain a diffusion tensor model value at each white matter voxel. We will further extract the mean FA value of a group of voxels that may identify regions with significantly different white matter fiber microstructure [55, 56].

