### Statistical analysis

We will use the IBM SPSS Statistics 24 [57] and R [58] to perform statistical analyses. Two-way repeated measures analysis of variance (ANOVA) will be used to compare the group effect. If subjects are lost to follow up, an intention-to-treat analysis will be conducted. Student’S *t* test will be used to compare the within-group changes when ANOVA reveals a significant difference. Statistical significance is determined by a two-sided *p* value of less than 0.05. In addition, if any demographic or clinical characteristics are significantly imbalanced, analysis of covariance will be performed to adjust the imbalance. To help prevent missing data, all questionnaires are user friendly and collected electronically, and all personnel related to the study are trained to identify and engage the subjects who are at the greatest risk of dropout during follow up. In cases of missing data, the method of baseline observation carried forward [59] will be used to impute these data from all enrolled subjects.

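### The article calls 30 per group sufficient for the three-modality MRI search, but its sample-size support covers one two-group comparison at 0.05 and its only significance rule is not adapted to region-wise testing

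*Protocol article*

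**What the plan says.** **Sample size.** The section Sample size considerations states the design parameters ("We assumed a two-tailed comparison"; "set the type I error rate at 0.05 with 80% power") and reports that "the effect size is calculated as 0.74". It then adds that "there is evidence from a small sample (8 subjects) that VR-enhanced treadmill training" for 5 sessions per week over 3 weeks led to significant cerebral reorganization. From these two supports it concludes that 30 per group is enough both for the effectiveness comparison and for studying brain mechanisms with three MRI modalities.

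**Imaging search.** MRI data processing takes 14 subcortical regions and structural connectivity over 360 cortical parcels and says "we will find ROIs that may correlate with rehabilitation performance and continuing performance". It adds a grey-matter density analysis looking for significant local differences, a count of functional links for each voxel, and diffusion imaging: "We will further extract the mean FA value of a group of voxels that may identify regions with significantly different white matter fiber microstructure". Secondary outcome measures says that correlations between brain parameters and clinical outcomes will be tested. It points to regions tied to motor learning and control, but does not list them or confine the search to them.

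**Significance rule.** Statistical analysis gives one rule: "Statistical significance is determined by a two-sided *p* value of less than 0.05". It is not limited to any outcome, and the article gives no other threshold.

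**The concern.** The sufficiency statement is a positive claim in the published text. A power calculation for one comparison says nothing about finding regions among several hundred. A study of 8 people in treadmill training does not show that 30 per group can separate two upper-limb programmes on MRI.

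The article also calls imaging differences significant while defining that word only through a general 0.05 threshold. Read literally, chance alone would supply a list of regions. At stake is the second half of the stated aim, the brain mechanism of recovery, for which each subject is scanned three times.

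**Working it through.** **Inputs.** Two-sided alpha 0.05, 80% power, 80 randomized with 25% dropout, effect size 0.74, and the 8-subject study are all from Sample size considerations. Allocation is 1:1 (Study design: "They will be randomized in a 1:1 fashion into"). The 14 regions and 360 parcels are from MRI data processing. The article does not give the number of imaging tests. I assume one test per region or parcel: 14 + 360 = 374.

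**1. The plan's own figure.** Completers: 80 × (1 − 0.25) = 60, or 30 per group. For a two-sample t test with 58 degrees of freedom and noncentrality d × √(30/2), power of 80% at two-sided 0.05 requires d = 0.736, which rounds to the stated 0.74. Power at d = 0.74 is 80.5%. The figure is correct for one comparison. No outcome, modality or standard deviation is attached to it.

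**2. Chance findings if 0.05 is applied to each region and nothing is related.** Expected number = m × 0.05. Chance of at least one, if the tests are independent = 1 − 0.95^m.

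| Tests (m) | Expected by chance | At least one |
|---|---|---|
| 14 | 0.7 | 51% |
| 374 | 18.7 (95% range 11 to 27) | > 99.99% |
| 748 (374 × 2 performance measures) | 37.4 | > 99.99% |

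**3. Dependence between regions.** Brain regions are correlated, so independence is too simple. The table summarises 20,000 simulated sets of 374 null statistics with a common correlation.

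| Correlation | Mean | Median | 90th percentile | At least one |
|---|---|---|---|---|
| 0 | 18.7 | 19 | 24 | every run |
| 0.2 | 18.8 | 15 | 34 | every run |
| 0.5 | 18.9 | 7 | 49 | 97% |
| 0.8 | 18.8 | 0 | 52 | 48% |

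The expected number does not depend on the correlation; the small differences in the mean are simulation error. The spread does depend on it. With strong correlation many studies would show nothing and some would show dozens of regions.

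**4. What 30 per group supports once the search is corrected.** Bonferroni is used here because it can be computed without the imaging data. It is the strict end; false discovery rate or permutation control would cost less.

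| Tests | Alpha per test | Detectable d at 80% power | Power at d = 0.74 |
|---|---|---|---|
| 1 | 0.05 | 0.74 | 80% |
| 14 | 0.05/14 = 0.0036 | 1.01 | 44% |
| 374 | 0.05/374 = 0.000134 | 1.28 | 13% |

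For correlations, the detectable r is tanh[(z for alpha + z for power)/√(n − 3)]. Going from one test to 374, it rises from 0.355 to 0.549 with both groups pooled (n = 60), and from 0.492 to 0.715 within one group (n = 30).

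**The case against.** The strongest reply is that the article never says 0.05 is applied uncorrected to each map. The rule follows directly on the ANOVA and t tests, in a section that does not mention imaging, and MRI data processing describes pipelines rather than thresholds. Imaging corrections are often left to an analysis plan, which is not shown here. The aim is worded as exploratory, MRI is secondary, and the Discussion names limited sample size as a limitation.

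Most of this stands, and it rules out several stronger readings that a reader might infer:

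- **That the trial will report many false regions.** This depends on no correction being used and few associations being real. Under strong dependence the typical count could be low.
- **That all 360 × 359/2 = 64,620 parcel pairs are tested, giving about 3,231 chance findings.** The wording on connectivity is ambiguous and does not say so.
- **That regions are selected and then re-tested in the same subjects.** The text describes selecting regions, extracting mean values and testing correlations, and mentions only one cohort. It does not state a second test.
- **That sufficiency is claimed from the treadmill study alone.** The 0.74 calculation comes first and the small study is added to it.

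The reply does not rescue the sufficiency statement. That is an assertion, not an omission, and an unseen plan cannot supply the support it lacks. Calling the aim exploratory also sits badly with declaring the sample adequate for it. Nor does the position of the 0.05 rule settle its scope: it is worded without restriction, and the imaging text uses significance with no other definition.

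**Conclusion.** The point holds in two parts of unequal strength.

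The firm part is that the MRI half of the sufficiency statement is unsupported. The 0.74 figure is right for one two-group comparison and for nothing wider. Even over the 14 subcortical regions alone, Bonferroni brings power at 0.74 to 44%; over 374 regions it is about 13%. These are worst-case figures for a corrected search and assume usable scans from all 30 in each group.

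The conditional part is that, if the general rule is applied as written and no association is real, about 19 of 374 region tests would be significant by chance. This rests on one test per region. The mean holds under any dependence, but the count in a single study could vary widely. If the analysis plan already controls imaging error, this part reduces to a missing cross-reference.

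The primary Fugl-Meyer comparison is unaffected. The correction should be made because the mechanism findings are half of the stated aim.

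**What to change.** 1. In Sample size considerations, withdraw the MRI part of the sufficiency statement, or qualify it so that 30 per group is called sufficient only for a single two-group comparison at two-sided 0.05.
2. In Statistical analysis, state that the unadjusted 0.05 rule does not cover region-wise or voxel-wise imaging tests. Exempting imaging is better than confining the rule to the primary outcome, which would leave the secondary clinical scales with no rule.
3. Use permutation-based family-wise error control for voxel-wise maps and false discovery rate control within each modality for parcels and connections. Alternatively, test a short list of motor regions named in advance.
4. Report effects in regions selected on the same data as descriptive and hypothesis-generating.

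The cost is wording and analysis settings, with no new data, visits or scans. The downside is that fewer regions will be called significant, and real but moderate effects may be missed. A short pre-named list limits that loss.

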### Statistical analysis

We will use the IBM SPSS Statistics 24 [57] and R [58] to perform statistical analyses. Two-way repeated measures analysis of variance (ANOVA) will be used to compare the group effect. If subjects are lost to follow up, an intention-to-treat analysis will be conducted. Student’S *t* test will be used to compare the within-group changes when ANOVA reveals a significant difference. Statistical significance is determined by a two-sided *p* value of less than 0.05. In addition, if any demographic or clinical characteristics are significantly imbalanced, analysis of covariance will be performed to adjust the imbalance. To help prevent missing data, all questionnaires are user friendly and collected electronically, and all personnel related to the study are trained to identify and engage the subjects who are at the greatest risk of dropout during follow up. In cases of missing data, the method of baseline observation carried forward [59] will be used to impute these data from all enrolled subjects.

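### The between-group test is fixed as the group effect of a repeated measures ANOVA; read literally with week 0 in the response, it dilutes the treatment contrast and does not match the two-group power calculation

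*Protocol article*

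**What the plan says.** The Statistical analysis section names one between-group test: "Two-way repeated measures analysis of variance (ANOVA) will be used to compare the group effect". Within-group t tests follow if the ANOVA is significant, and analysis of covariance is added only when a characteristic is significantly imbalanced.

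The Study design section lists three assessments. The first is "immediately following enrollment but before randomization (week 0"); the others are at weeks 3 and 15.

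The Sample size considerations section rests on a different comparison: "This randomized controlled trial is a two-group independent design". It continues "We assumed a two-tailed comparison and set the type I error rate at 0.05 with 80% power", reports that "the effect size is calculated as 0.74, which is between a medium (0.5) and large (0.8) effect size", and concludes that "30 subjects for one group is sufficient to assess the effectiveness of immersive VR training".

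The end of the Secondary outcome measures section adds that the stroke-related secondary scales, which include Brunnstrom stage and NIHSS, will be considered as covariates for the primary outcome. The week-0 Fugl-Meyer arm score is not among them.

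**The concern.** The trial asks whether immersive VR improves upper-limb recovery more than conventional training does. In a group-by-time repeated measures ANOVA, the group effect is the between-subject main effect. With balanced data it is the same as a t test on each patient's average over all visits.

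If week 0 is one of those visits, two things follow. The expected difference at week 0 is zero by randomisation, so a constant post-treatment effect shrinks to two thirds of its size. Stable differences between patients also stay in the error term, because the main effect uses no change from baseline.

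This is the only between-group test stated for the primary outcome. Followed to the letter, it could well miss the effect the trial was sized to detect.

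**Working it through.** **Inputs from the protocol article.** Two-sided alpha 0.05, 80% power, d = 0.74 and 30 per arm (Sample size considerations); visits at weeks 0, 3 and 15 (Study design).

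**Assumptions, not in the documents.** Complete data, unit SD at each visit, compound symmetry with between-visit correlation rho, expected differences (0, 0.74, 0.74), and no covariates. No correlation is given, so rho from 0.5 to 0.9 is shown.

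**Step 1: the plan's own figure.** For a two-sample t test (noncentral t, 58 df) with 30 per arm, the effect detectable with 80% power is 0.736, which rounds to 0.74. Power at exactly 0.74 is 80.5%. The stated figure is reproduced.

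**Step 2: the literal group effect.**
- Difference in three-visit means: (0 + 0.74 + 0.74)/3 = 0.493.
- SD of one patient's three-visit mean: sqrt((1 + 2 rho)/3).
- Effective size: 0.493 / sqrt((1 + 2 rho)/3), put into the same t test.

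| rho | SD of mean | effective d | power | completers per arm for 80% |
|---|---|---|---|---|
| 0.5 | 0.816 | 0.604 | 63% | 44 |
| 0.7 | 0.894 | 0.552 | 56% | 53 |
| 0.9 | 0.966 | 0.511 | 49% | 62 |

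A simulation of 40,000 trials per row gave 63%, 55% and 49.5%.

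**Step 3: where the loss disappears.** The effective size equals 0.74 when (1 + 2 rho)/3 = (2/3)^2 = 4/9, that is, rho = 1/6, about 0.17. Below that, the main effect keeps 80% power or more (90% at rho = 0). Above it, power is lost.

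**Step 4: other tests on the same data.**
- Mean of weeks 3 and 15 without baseline, variance (1 + rho)/2.
- The same mean adjusted for week 0, residual variance (1 + rho)/2 - rho^2. At rho = 0.7 this is 0.85 - 0.49 = 0.36, so the effective size is 0.74/0.6 = 1.23.
- Group-by-time interaction, F with 2 and 116 df and noncentrality (30/2) x (2/3) x 0.74^2 / (1 - rho). At rho = 0.7 this is 15 x 0.365 / 0.3 = 18.25.

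| rho | group main effect | mean of weeks 3 and 15 | same, adjusted for week 0 | interaction |
|---|---|---|---|---|
| 0.5 | 63% | 90% | 98% | 84% |
| 0.7 | 56% | 86% | 99.7% | 97% |
| 0.9 | 49% | 82% | nearly 100% | nearly 100% |

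The second and third columns differ only in whether week 0 is in the response, so that is what costs the power.

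**Step 5: if the effect is not sustained.** With half the effect left at week 15, the main effect has 41% to 31% power for rho 0.5 to 0.9. With an effect at week 3 only, it has 21% to 16%.

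**The case against.** **The text may mean the interaction.** It never says main effect and never lists the levels of time. The t tests of within-group change that follow a significant ANOVA fit a time or interaction result better than a difference in three-visit means. On that reading there is no loss at rho of 0.5 or more. This stands as a reason to state the power loss conditionally. It does not rescue the wording: no section mentions an interaction, and the ANOVA output has separate rows for group, time and group by time. Nor is this detail merely left to an analysis plan, because the article does name the term.

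**Covariates may be used.** The covariate sentence under Secondary outcome measures could recover some power. If covariates explained an assumed 30% to 50% of the variance of the three-visit mean, power would be 79% to 90% at rho 0.5, 71% to 84% at rho 0.7 and 64% to 79% at rho 0.9. The sentence is loose and omits the week-0 arm score, but 63% to 49% is the no-covariate case and must be labelled so.

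**The calculation uses 60 completers.** The plan randomises 80 and intends an intention-to-treat analysis. With 40 full records per arm, the main effect has 76% to 62% power at rho 0.5 to 0.9. With a quarter of patients carried forward from baseline it is roughly 47% to 39%, but that mixes in the imputation rule, a separate matter.

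**A stronger reading to avoid.** A reader might infer that the test produces false positives from chance baseline differences. In null trials selected for a non-significant baseline difference above 0.4 SD (about 7% of trials), rejection does rise to roughly 14% to 18%. Over all trials it is 5%, as for any valid unadjusted comparison, so the documents do not support a claim of inflated type I error.

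**Conclusion.** The concern holds in conditional form. The article names a term that, read literally with the three scheduled assessments as time levels, does not test recovery after baseline and does not correspond to the comparison behind the sample size. That reading is the natural one, since nothing removes week 0 from the response, but it is not stated outright.

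Under the listed assumptions, the loss against the 80.5% of the sized comparison is about 17 to 31 percentage points for rho 0.5 to 0.9. It vanishes at rho of about 0.17 or lower, shrinks if useful covariates are fitted, and grows if the effect fades by week 15. It would be wrong to say flatly that the trial has 50% power: that rests on a correlation, an effect pattern and a reading that the article does not supply. If the interaction was intended, the defect is one of wording, but it still leaves the decisive term open to choice once data are seen.

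**What to change.** In the Statistical analysis section, replace the purpose clause of the ANOVA sentence with a test that takes week 0 out of the response. Suggested content: the Fugl-Meyer arm motor scores at weeks 3 and 15 are the responses in a repeated measures model with group, visit, group by visit and the week-0 score as covariate; the treatment effect is the adjusted between-group difference.

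If the three-visit ANOVA is kept, state that the group-by-time interaction is the test of treatment and that the group main effect is not.

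Either change costs one or two sentences before unblinding. It needs no new data, visits or patients, and both models run in the SPSS and R software already named.

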### Secondary outcome measures

We will apply MRI techniques to assess the performance of immersive VR-based rehabilitation and to investigate the brain mechanisms of rehabilitation, particularly in regions related to motor learning and motor control. Three different MRI modalities will be acquired: (1) high-resolution anatomical MRI (T1-MRI) for estimating anatomical parameters of cortex, subcortex, and structural connectivity; (2) resting-state functional MRI (RS-fMRI) for estimating the functional connectivity of brain regions; and (3) diffusion tensor imaging (DTI) for estimating tractographic parameters of white matter and the microstructure of gray matter. Each subject will be scanned three times (before rehabilitation, immediately following 3 weeks of rehabilitation, and 12 weeks post-rehabilitation). The brain parameters obtained by MRI will be assessed and correlation with the clinical outcome measures will be tested.

Other secondary outcome measures include: (1) Brunnstrom stage scores, which will be obtained for assessment of motor recovery of the upper extremities; (2) assessment of the subject’s’ mental state, which will be determined using the Hamilton Depression Scale (HAMD) [42] and the Hamilton Anxiety Scale (HAMA) [43]; (3) the activities of daily living (ADL), which will be determined using the Function Independent Measure (FIM) [44] and the Bathel Index (BI) [45]; (4) assessment of the severity of ischemic stroke and cognitive function, which will be determined using the National Institutes of Health Stroke Scale (NIHSS) [46] and the Korea-Mini Mental Status Evaluation (K-MMSE) [38], respectively. These stoke-associated measures will also be evaluated as covariates in regard to the primary outcome measure.

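### Covariate adjustment hinges on significant baseline imbalance, which practically shuts out the balancing factors, while a second section lists outcomes as covariates without limiting them to baseline

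*Protocol article*

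**What the plan says.** Three places in the protocol article bear on adjustment.

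- **Statistical analysis.** The group comparison is a two-way repeated measures ANOVA, with no covariate named. Adjustment is conditional: "if any demographic or clinical characteristics are significantly imbalanced, analysis of covariance will be performed to adjust the imbalance".
- **Study design.** Allocation uses "stratified, permuted block randomization with a block size of 8 and balanced by age and location of stroke". Nothing in the article carries these two factors into the model. Assessments are at weeks 0, 3 and 15.
- **Secondary outcome measures.** After listing Brunnstrom stage, the Hamilton depression and anxiety scales, FIM, Barthel Index, NIHSS and K-MMSE, the section adds: "These stoke-associated measures will also be evaluated as covariates in regard to the primary outcome measure". It gives no time point and no imbalance condition.

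**The concern.** In a randomised trial, a baseline significance test asks whether chance produced a difference. It does not ask whether the variable predicts the outcome. A rule built on it can bring in a variable of no prognostic value and leave out a strong one, and the final model is known only after the data are seen. Factors balanced by design are the ones least likely to pass such a test, yet they are the ones the analysis should carry.

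The two sections also disagree. One makes adjustment conditional; the other lists covariates unconditionally. The listed measures are outcomes too, recorded again after treatment. Some of them, Brunnstrom stage in particular, track the same arm recovery as the primary outcome. Adjusting for a post-treatment value of such a measure could absorb part of the treatment effect.

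At stake are the precision of a trial of 60 completers and a primary model that a reader can identify in advance.

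**Working it through.** **Inputs from the protocol article (Sample size considerations).** 30 completers per group, two-sided alpha 0.05, 80% power, standardised effect 0.74. The section also labels 0.5 a medium effect.

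**Assumed, because the article gives no figure.** Correlation r between baseline and later Fugl-Meyer of 0.5 to 0.8, equal variances, effects in SD units, two levels each for age and stroke location.

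**1. The plan's own figure.** The article states that "the effect size is calculated as 0.74". For a two-sample t test (noncentral t, 30 per group, two-sided 0.05, 80% power) the detectable effect is 0.736, so 0.74 is reproduced. It uses no covariate.

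**2. What the trigger lets through.** With 30 per arm, a baseline difference counts as not significant up to t(0.975, 58) × √(2/30) = 2.002 × 0.258 = 0.517 SD.
- If the default analysis compares post-treatment scores, an imbalance at that limit shifts the estimate by 0.517 × r = 0.36 SD at r = 0.7.
- If the default is a change-type analysis, the shift is 0.517 × (1 − r) = 0.16 SD at r = 0.7.

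**3. How often it fires.**
- One unstratified variable: 5%.
- At least one of k independent characteristics: 1 − 0.95^k, which is 23% for k = 5, 34% for k = 8 and 40% for k = 10.
- Age as a balancing factor, in strata with blocks of 8: significantly imbalanced in 0 of 4,000 simulated trials of 60.

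**4. Cost in power.** Power comes from the noncentral t with noncentrality (d/f) × √(30/2), where f is the residual SD relative to the raw SD:
- post-treatment comparison, f = 1;
- change-type test, f = √(2(1 − r));
- analysis of covariance on baseline, f = √(1 − r²).

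| d | r | Post-treatment | Change-type | Baseline-adjusted |
|---|---|---|---|---|
| 0.5 | 0.5 | 48% | 48% (f = 1.00) | 59% (f = 0.87) |
| 0.5 | 0.7 | 48% | 69% (f = 0.77) | 76% (f = 0.71) |
| 0.74 | 0.5 | 80% | 80% | 90% |
| 0.74 | 0.7 | 80% | 95% | 98% |

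Simulation agrees to within about two points. At d = 0.5, for r = 0.5 and 0.7 respectively, the change-type test has 50% and 68% and the baseline-adjusted test 59% and 75%. Applying the trigger to baseline Fugl-Meyer, with a post-treatment default, leaves power at about 48% for both r. The rule therefore recovers almost none of the available gain.

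**5. Type I error.**
- The trigger with a post-treatment default gives 4.4%, 3.9% and 3.1% overall at r = 0.5, 0.7 and 0.8. All are below 5%.
- A group-by-time test gives 4.7% to 5.0%.
- Leaving out balancing factors that explain an assumed 20% of the variance gives about 3.1%.
- Among trials where baseline Fugl-Meyer differs with p between 0.05 and 0.2, the unadjusted post-treatment test rejects in 8.7% to 12.6% of null trials, against about 5% with baseline adjustment. The rule leaves those trials uncorrected even though the overall rate is conservative.

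**The case against.** The strongest reply is that the planned analysis is a repeated measures ANOVA, not a bare post-treatment comparison. If week 0 is a level of the time factor and group-by-time is tested, baseline Fugl-Meyer is already partly used. A reader might infer that baseline is simply ignored and that 27 points of power (48% against 75% at r = 0.7) are lost. The article does not support that, because it does not say which term is tested or whether week 0 is included. Under the change-type reading the gap at d = 0.5 is roughly 6 to 10 points, and at the plan's own 0.74 with r = 0.7 almost nothing is lost (95% against 98%). This part of the objection stands.

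Three other strong readings also fail.
- **Covariates enter only on imbalance.** This is true of the Statistical analysis section alone. The Secondary outcome measures section adds covariates unconditionally. If those are baseline values, several are plausible prognostic factors.
- **The treatment effect will be adjusted away.** The article never says that post-treatment values will be used; a baseline reading is natural. If a post-treatment measure carried the same 0.74 SD effect and correlated 0.8 with Fugl-Meyer, 0.74 × (1 − 0.8) = 0.15 SD would remain. The article gives neither input, so this only illustrates why the time point must be stated.
- **False positives are inflated.** Every overall rate found is at or below 5%.

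It can also be said that the full model belongs in an analysis plan that is not shown. That excuses silence. It does not excuse the trigger, which is stated, or the unrestricted covariate list, which is stated too.

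**Conclusion.** The concern holds in a limited form. The trigger chooses covariates by chance, practically never admits the two factors that balance the allocation, and makes the model depend on the data. The separate covariate list conflicts with it and does not exclude post-randomisation values.

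The consequence is lost precision, with conservative overall type I error. Against always adjusting for baseline Fugl-Meyer, at 30 per arm and d = 0.5, the loss is about 11 points (r = 0.5) to 27 points (r = 0.7) if the default is a post-treatment comparison. It is roughly 6 to 10 points if the default is a change-type group-by-time test. These sizes rest on the assumed r and on an ANOVA term that the article leaves open. The near-zero chance of age triggering adjustment rests on two-level factors tested as categories; age tested as a continuous variable could still differ within its categories.

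This should be changed. It does not undermine the design, and the sample size needs no increase on its account.

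**What to change.** - Delete the significance trigger and the baseline tests that feed it.
- Pre-specify baseline Fugl-Meyer, age and location of stroke as covariates in the primary model, whatever the observed balance. Week 0 then serves as a covariate, not also as a level of the time factor. Days since onset may be added but is optional.
- In Secondary outcome measures, name which listed measures are covariates and restrict them to their baseline values. Treat week-3 and week-15 values as outcomes only. This also reconciles that section with Statistical analysis.

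The change is wording only. All the variables are already collected, and the price is a few degrees of freedom.
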